### Outcomes

#### Primary outcome

The primary outcome measure will be self-reported physical function, measured by the PSFS^56 77^ at baseline, 6, 12 and 52 weeks after randomisation. The primary time-point is 6 weeks after randomisation (ie, immediate post-intervention), while the secondary time-points are 12 and 52 weeks after randomisation. The PSFS, originally proposed by Stratford *et al*,^77^ is a valid, reliable and responsive self-report instrument^56^ designed to assess functional change in people with musculoskeletal disorders. Participants identify three important activities they are unable to do or have difficulty with because of their LBP and rate their ability to perform each activity. Each activity is rated on an 11-point numerical rating scale ranging from 0=‘unable to perform activity’ to 10=‘able to perform the activity at preinjury level’. The total score, calculated by summing the numerical ratings for each activity, is provided on a discrete scale ranging from 0 to 30, where higher scores indicate better function.

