#### Secondary outcomes

Secondary outcome measures will be grouped into domains and will include:

Symptoms and function:

Pain intensity, measured by the Numeric Rating Scale (NRS)^78^ at baseline, 6, 12 and 52 weeks after randomisation.Pain frequency, measured by a self-reported question at baseline, 6, 12 and 52 weeks after randomisation.Disability, measured by the Roland-Morris Disability Questionnaire (RMDQ)^56 79^ at baseline, 6, 12 and 52 weeks after randomisation.

Quality of life and general health:

Health-related quality of life (HRQoL), measured by the EuroQol 5-Dimension 5-Level (EQ-5D-5L)^80^ at baseline, 6, 12 and 52 weeks after randomisation.Sleep quality, measured by the Pittsburgh Sleep Quality Index (PSQI)^81 82^ at baseline, 6, 12 and 52 weeks after randomisation.Consumption of highly processed food, measured by the Short Screening Questionnaire of Highly Processed Food Consumption (sQ-HPF)^64^ at baseline, 6, 12 and 52 weeks after randomisation.

Health behaviours and beliefs:

Exercise importance, measured by a self-reported question at baseline and 6 weeks after randomisation. Participants indicate how important it is to them to do regular exercise to manage their back condition. Answer options are presented on a 7-point Likert-type scale ranging from 1=‘not at all important’ to 7=‘extremely important’, where higher scores indicate higher importance.Exercise self-efficacy, measured by the Self-Efficacy for Exercise (SEE) Scale^83^ at baseline, 6, 12 and 52 weeks after randomisation.Adherence to exercise recommendations, measured by the Exercise Adherence Rating Scale (EARS)^84^ at 6 weeks after randomisation.

Healthcare utilisation and engagement:

Co-intervention use, measured by a self-reported questionnaire specifically designed for this study at baseline, 6, 12 and 52 weeks after randomisation.Health literacy level, measured by the Health Literacy Questionnaire (HLQ)^85^ at baseline, 6, 12 and 52 weeks after randomisation.

Patient perception of change:

Global perceived effect, measured by the Global Perceived Effect (GPE) scale^86^ at 6, 12 and 52 weeks after randomisation.Impression of change in overall status, measured by the Patient’s Global Impression of Change (PGIC)^87^ at 6, 12 and 52 weeks after randomisation.

Satisfaction and usability of the app:

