#### Other measures

Smallest Worthwhile Effect^88^ in function, measured at baseline. Participants will be asked to nominate the smallest score in the PSFS (total and for each activity) they would need to achieve to consider the costs, risks and inconveniences of using a mobile application intervention worthwhile.Adverse events, collected through a self-reported form at 2, 4, 6 and 52 weeks after randomisation.

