### Statistical methods

All statistical analyses will be conducted following the intention-to-treat principle. Baseline characteristics will be summarised by arm using descriptive statistics and reported with measures of frequency (proportion), mean, SD and 95% CI. Differences in dichotomous variables will be expressed as risk difference and number needed to treat or number needed to harm with 95% CI. Continuous variables will be summarised and reported with mean and SD in case of a Gaussian (normal) distribution or as the median and IQR in case of a skewed distribution.

At the interim and final analysis, differences in outcome data between each intervention arm and the control group will be analysed using the Student’s t-test in the case of a Gaussian (normal) distribution. Otherwise, the non-parametric Mann-Whitney U test will be used after correcting for baseline differences, if required. Changes in health-related quality of life scores will be analysed using the Wilcoxon test. The Cox proportional hazards regression modelling will be used to adjust for potential confounding factors. For all analyses, statistical significance will be indicated by a p value <0.05.

A planned hypothesis-generating (exploratory) subgroup analysis will be conducted considering diet and sleep. Interaction models will compare the effectiveness of the sleep module in people with low and high scores on the PSQI, as well as the diet module in people with low and high scores on the sQ-HPF. Additionally, a planned exploratory analysis will be conducted to investigate the potential impact of adherence on the magnitude of the treatment effects.

The interim analysis will be conducted after completion of the 6-week intervention programme by the first 25 participants in each arm. Whether and how the trial will continue will be determined by the outcome of the interim analysis, which will allow dropping intervention arms that are deemed futile, in accordance with the following prespecified decision rules considering the primary endpoint (ie, change in mean PSFS score from baseline to 6 weeks after randomisation):

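### Cox regression is the only model named for confounder adjustment, yet the article defines no time-to-event outcome to which it could apply

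*Protocol article*

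**What the plan says.** Under Statistical methods, each intervention arm is compared with control at the interim and final analyses. Outcome differences "will be analysed using the Student’s t-test in the case of a Gaussian (normal) distribution", with the Mann-Whitney U test as the alternative and a Wilcoxon test for quality of life. The next sentence, not tied to any outcome, is "The Cox proportional hazards regression modelling will be used to adjust for potential confounding factors". A general 5% significance threshold follows.

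The outcomes are defined as follows.
- **Primary outcome:** the PSFS total "is provided on a discrete scale ranging from 0 to 30, where higher scores indicate better function". The endpoint for the interim decision is "change in mean PSFS score from baseline to 6 weeks after randomisation".
- **Secondary outcomes:** scales and self-report items at fixed visits, for example "Pain intensity, measured by the Numeric Rating Scale (NRS)^78^ at baseline, 6, 12 and 52 weeks after randomisation". Some are taken at fewer visits.
- **Dichotomous variables:** "Differences in dichotomous variables will be expressed as risk difference and number needed to treat or number needed to harm with 95% CI".
- **Adverse events:** "Adverse events, collected through a self-reported form at 2, 4, 6 and 52 weeks after randomisation". The Harms section says they are reported by type and by the proportion of participants affected.

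**The concern.** A Cox model needs an event, a time from a defined origin to that event, and a rule for participants in whom it is not observed. It returns a hazard ratio. The trial's outcomes are values recorded at scheduled visits, and its effect sizes are in PSFS points or risk differences.

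At stake is the covariate-adjusted analysis. Taken literally, the sentence gives no adjusted difference in PSFS points. Analysts would have to depart from the protocol and choose another model, or invent an event definition. Either choice could be made after the data have been seen, in a trial with four comparisons against control. The article therefore prespecifies no usable model for adjusting the PSFS comparison.

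**Working it through.** **1. Match the named model to each class of outcome.**

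| Outcome class (section) | What is recorded | Event time defined? |
|---|---|---|
| PSFS (Primary outcome) | 0–30 total at baseline, 6, 12 and 52 weeks | No |
| Secondary outcomes | Scores, Likert ratings and self-report items at some or all of the same visits | No |
| Process measures | Counts, percentages and rates | No |
| Smallest worthwhile effect (Other measures) | PSFS score nominated at baseline | No |
| Adverse events (Other measures, Harms) | Form at weeks 2, 4, 6 and 52; proportions reported | No |

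Data collection methods says that the timing of any withdrawal is recorded, but withdrawal is not listed as an outcome. No hazard ratio is mentioned anywhere.

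**2. See whether the sample size depends on Cox.** The inputs in the Sample size section are a difference of 4 points, SD 5.8, two-sided 5%, 80% power, a Dunnett-type comparison of four arms with control, and 21 + 42 = 63 evaluable per arm.
- Standardised difference: 4 / (5.8 × √(2/63)) = 4 / 1.033 = 3.87.
- Two-sided Dunnett critical value for four comparisons with a shared control (simulated, correlation 0.5): 2.44.
- Power to reject all four comparisons: 0.793 at 63 per arm and 0.803 at 64 per arm, so 63 agrees with the stated 80% to within rounding. The interim dropping rules were not modelled.
- Totals: 5 × 63 = 315; 315 / 0.85 = 370.6; 5 × (25 + 49) = 370.

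The stated figures are thus reproduced from a difference in means alone. The two dropping rules, at 0.5 and 4 points, are also differences in mean PSFS change. Neither uses a hazard ratio.

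**3. See what Cox returns if it is forced onto these data.**

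*Fixed 6-week visit as the time, everyone counted as an event.* All N times are tied and the risk set is everyone. The Breslow score for the arm indicator x at β = 0 is Σxᵢ − N·x̄ = 0, so the estimated log hazard ratio is 0 whatever the PSFS values are. Simulation agreed: 0.000 in each of 100 runs with a true effect of 4 points.

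*PSFS score used as the time.* The simulation assumed 63 per arm, baseline mean 12 and SD 5, a follow-up score of 8 + 0.5 × baseline + 4 × arm + error with SD 5.2, rounded and held within 0–30. The mean log hazard ratio was −0.695, so the hazard ratio is exp(−0.695) = 0.50. That number has no reading in PSFS points and cannot be set against the 4-point effect.

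*Binary outcome with constant time, non-events censored.* Without covariates, with d₁ events among n₁ and d₀ among n₀, the Breslow score equation is d₁ = (d₁ + d₀) · n₁e^β / (n₁e^β + n₀), which gives e^β = (d₁/n₁) / (d₀/n₀). This is a risk ratio. The protocol reports risk differences and numbers needed to treat, and it describes no such device.

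The simulated values are illustrations under the stated assumptions. The conclusion rests on step 1.

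**The case against.** The strongest reply is that little depends on the sentence. In an individually randomised trial, adjustment for confounders is supportive. The between-arm test is a t-test or Mann-Whitney test, the dropping rules use unadjusted differences in change, and the sample size uses a mean difference. This stands, and it limits the severity.

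A reader might infer that the adjusted analysis cannot be run at all. That goes too far. The software can be made to run, and constant-time Cox on a binary outcome returns a risk ratio. The difficulty is that the result is not the quantity the protocol reports, and that no such use serves the PSFS score.

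A reader might also infer that every adjusted result in the trial is affected, or that no other adjustment is mentioned. The article does not say which outcomes will be adjusted. It also mentions a correction for baseline differences with the Mann-Whitney test, without a method, and interaction models for the exploratory sleep and diet subgroups. Cox is the only regression model named for confounders, but not the only reference to adjustment.

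Finally, the full statistical analysis plan is unpublished and may name a suitable model. That would not cure the article, because the point is a wrong statement and not an omitted detail. A valid model in the plan would contradict this sentence.

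**Conclusion.** The point holds in a limited form. The one regression model named for covariate adjustment fits no outcome the article defines, and it cannot produce an adjusted PSFS mean difference. This should be fixed. The documents do not support the stronger reading that the primary comparison, the interim decisions or the sample size are compromised, since all three rest on unadjusted PSFS comparisons. The size of the problem is therefore the loss of a usable prespecified adjusted analysis, with no change to any stated figure. The conclusion assumes that the outcome list in the article is complete and that the Cox sentence is meant for those outcomes, because no other is named.

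**What to change.** Replace the Cox sentence along these lines.
- **Continuous scores, including PSFS:** linear regression, either ANCOVA at 6 weeks or a mixed model across the 6-, 12- and 52-week visits. Adjust for the baseline value and prespecified baseline covariates, and report adjusted mean differences with 95% CIs. Baseline PSFS is already collected, and the estimate can be read directly against the 4-point effect. Adjusting for a prognostic baseline score should also improve precision.
- **Binary outcomes:** a model that yields the risk difference the protocol reports, such as an identity-link binomial model, or logistic regression with marginal standardisation. Logistic coefficients alone give odds ratios and log-binomial coefficients give risk ratios, so naming either without that step would leave a mismatch.
- **If a time-to-event outcome was intended:** define the event, time origin and censoring rule, and confine Cox to that outcome.

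The cost is one sentence in the protocol, submitted through the ethics amendment route described under Protocol amendments, and a check that the unpublished analysis plan agrees. No extra data or participants are needed. The change is best made before outcome data are analysed by arm.

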### Trial design and setting

This study will be a parallel, superiority, decentralised, adaptive RCT encompassing a MAMS design with individual randomisation in a 1:1:1:1:1 ratio. The trial protocol has been designed according to the Standard Protocol Items: Recommendations for Interventional Trials (SPIRIT) statement,^44^ and the interventions are reported according to the TIDieR-telehealth checklist,^45^ an extension of the Template for the Intervention Description and Replication (TIDieR) checklist. The trial will be conducted and reported according to the Adaptive Designs CONSORT Extension (ACE) statement,^46^ an extension of the Consolidated Standards of Reporting Trials (CONSORT) statement.

The clinical trial will be conducted entirely online in a community setting in Australia. Recruitment, consent, eligibility assessment, enrolment, intervention delivery and data collection procedures will be performed remotely using digital technology. The intervention will be delivered via an app that participants will download via the app store according to their smartphone or tablet operating system (ie, Apple App Store or Google Play Store).

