### Sample size

The sample size calculation was conducted a priori, considering a MAMS design with five arms (one control arm and four intervention arms) and two stages that consist of one interim and the final analysis. The primary endpoint was established at 6 weeks post-randomisation (ie, immediate post-intervention). A smallest worthwhile effect on the PSFS score (0–30) of 4 points was chosen to estimate the sample size, considering the literature^76^ and the nature of the intervention (ie, a 6-week digital intervention with no face-to-face interaction).

The sample size calculation was based on a two-sided type I error of 5% (significance level), a power of 80% to control for a type II error and an SD of 5.8 using a generalisation of the power requirements for testing multiple active arms to one control group, as proposed by Dunnett.^92^ The calculation resulted in 21 participants per arm at the first stage and 42 participants per arm at the second stage, reaching a total sample size of 315 participants. Allowing for a loss to follow-up rate of 15% at 6 weeks, the study would require a total sample size of 370 participants (n=25 in the first stage and 49 in the second stage per group). This total sample represents the maximum number of participants that will be enrolled when all the intervention arms meet the criteria for being maintained through the second interim stage (ie, no arm is dropped after the interim analysis). Therefore, there is the possibility that the study terminates with a smaller sample size if, at the interim analysis, one or more intervention arms meet the criteria for being dropped. For instance, if one, two or three arms are dropped after the interim, the study sample will decrease to 321, 272 and 223, respectively.

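### Up to four arms are each tested against control at an unadjusted p<0.05 although the trial was sized on Dunnett's many-to-one basis, so the 5% type I error is not kept

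*Protocol article*

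**What the plan says.** The Sample size section of the protocol article plans for "five arms (one control arm and four intervention arms) and two stages that consist of one interim and the final analysis". It takes a two-sided type I error of 5% and describes the calculation as "using a generalisation of the power requirements for testing multiple active arms to one control group, as proposed by Dunnett".

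Statistical methods says that, at the interim and the final analysis, "differences in outcome data between each intervention arm and the control group will be analysed using the" Student's t-test, or the Mann-Whitney U test if the data are not normal. The same paragraph closes with the decision threshold: "For all analyses, statistical significance will be indicated by a p value <0.05". The abstract names the same two tests.

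No adjusted p-value, testing hierarchy or simultaneous interval is mentioned anywhere. The interim decisions use point estimates only. An arm goes if its advantage over control is 0.5 points or less, or if it trails another intervention arm by more than 4 points. There is no stopping for efficacy.

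**The concern.** Dunnett's method treats the comparisons with a shared control as one family. A 5% error attached to it is the chance of any false positive in that family. The tests in Statistical methods are ordinary two-sample tests, and 0.05 is applied to every one of them, so each comparison spends 5% by itself.

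The Objectives ask whether the app is effective and which combination of components works best. No formal success criterion is given, but a single arm crossing 0.05 would naturally be reported as evidence that the app works. With up to four chances, that claim is made falsely more often than the design's 5% implies. The sample size was also calculated for a stricter test than the one to be used.

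**Working it through.** **Inputs** (protocol article)
- Sample size: two-sided 5% error; "a power of 80% to control for a type II error and an SD of 5.8"; "A smallest worthwhile effect on the PSFS score (0–30) of 4 points was chosen to estimate the sample size"; 21 + 42 = 63 evaluable per arm, 5 × 63 = 315 in total.
- Trial design and setting: "individual randomisation in a 1:1:1:1:1 ratio". Equal arms give a correlation of 0.5 between any two contrasts with the shared control.
- Statistical methods: the two dropping rules, and no efficacy stop, so the interim spends no type I error.

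Normal approximation throughout. A dropped arm is assumed to make no claim.

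**1. Which basis reproduces the stated sample size?**

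The two-sided Dunnett critical value for four comparisons, correlation 0.5, is c = 2.442 (unadjusted p = 0.0146). Per arm, n = 2 × 5.8² × (critical value + 0.842)² / 4².

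| Basis | n per arm |
|---|---|
| Unadjusted 1.96, power for one comparison | 34 |
| Dunnett 2.442, power for one comparison | 46 |
| Dunnett 2.442, power to detect all four effects | 64 |
| Stated | 63 |

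The stated 63 is matched, within one participant per arm, by Dunnett's threshold with 80% power for all four effects together (79.3% at 63). The article does not say which power it means. Under the unadjusted test it prescribes, 63 is far more than the 34 needed for one comparison, and more than the 49 needed for all four.

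**2. Error if no arm is dropped**

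Under the global null, with k arms, the chance of at least one |Z| > c is

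1 − ∫ [Φ((c − x√0.5)/√0.5) − Φ((−c − x√0.5)/√0.5)]^k φ(x) dx.

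| Arms at final analysis | c = 1.96 |
|---|---|
| 2 | 9.1% |
| 3 | 12.5% |
| 4 | 15.6% |

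With k = 4 and c = 2.442 the result is 5.0%.

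**3. Error if both rules are always followed**

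Simulation of the two-stage design (21 then 42 per arm, SD 5.8, no true effect; separate runs of 300,000 or more):

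| | Unadjusted 0.05 | Dunnett 2.442 |
|---|---|---|
| At least one significant result | 7.3–7.4% | 2.4% |
| of which false benefit | 7.1% | 2.3% |

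In about 30% of these null trials no arm survives the interim. A two-sided 5% rule for the family implies about 2.5% false benefit, so 7.1% is nearly three times that (7.1 / 2.5 = 2.8).

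The dropping rules remove mainly false findings of harm. Without dropping, the chance of at least one false benefit is 1 − ∫ [Φ((1.96 − x√0.5)/√0.5)]⁴ φ(x) dx = 7.8%. With dropping it is 7.1%.

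**4. Power under the stricter test**

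The standardised effect at 63 per arm is 4 / (5.8 × √(2/63)) = 3.87.
- Unadjusted, per arm: Φ(3.87 − 1.96) = 97%.
- Dunnett, per arm: Φ(3.87 − 2.442) = 92%.
- Dunnett with both rules followed, per arm: about 91% if one arm works, about 89% if all four do.
- Dunnett, all four effects detected: about 79% without dropping, about 69% with it. The unadjusted test with dropping gives 78% on the same definition.

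**The case against.** The strongest reply has four parts.

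- **The article never says family-wise.** It cites Dunnett for power requirements, and the 0.05 could be meant for adjusted p-values, with the details in an unpublished analysis plan. It is true that the family-wise reading is an inference from the Dunnett basis. But the article is not silent: it names ordinary two-sample tests and one threshold for every analysis. An analysis plan that applied Dunnett's test would depart from that text as it naturally reads.
- **15.6% is not the planned design**, because arms meeting a rule are to be dropped. This is fair, and the figure should not stand alone. But perfect adherence still gives more than 5%, and adherence is not assured: under Data monitoring committee the board only makes recommendations, and Statistical methods calls the rules indicators of futility.
- **The power reassurance depends on the definition.** This stands. Power per arm stays well above 80%, but power to detect all four effects does not.
- **Dunnett at 2.44 is conservative if the rules bind.** Also true. With strictly binding rules, a critical value of about 2.14 (unadjusted p about 0.032) would give 5%. That is still stricter than 0.05.

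**Conclusion.** The concern holds. Sample size and Statistical methods fix two incompatible rules, and the one that decides significance does not keep the 5% error. Under the global null the chance of at least one significant comparison with control is about 7.3–7.4% if both dropping rules are always followed and 15.6% if all four arms continue. It exceeds 5% at both ends.

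This rests on reading the 5% as belonging to the family, as the Dunnett basis implies, and on equal arms, SD 5.8, 21 + 42 evaluable per arm and a normal approximation. The interim adds no inflation. Because the conflict lies in the rule for the primary conclusion, it must be corrected.

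**What to change.** In Statistical methods, replace the blanket threshold for the primary outcome along these lines:

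> At the final analysis an intervention arm is declared superior to control on the primary outcome only if its Dunnett-adjusted two-sided p-value is below 0.05. The family is the four arms that started the trial, however many remain (critical value about 2.44, unadjusted p about 0.0146). Simultaneous 95% confidence intervals are reported. The interim uses only the point-estimate rules and makes no claim of significance. Elsewhere, 0.05 is nominal.

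If the Mann-Whitney branch is used, comparing its unadjusted p-value with 0.0146 is approximately right; Bonferroni's 0.0125 is a simple alternative. Another named procedure with strong control would also serve. A value near 2.14 is defensible only if the dropping rules are made strictly binding. The remaining option is to declare and justify a 5% error per comparison and remove the Dunnett basis from Sample size.

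The choice must be fixed before unblinded final results are seen. The cost is one paragraph in the protocol and the analysis plan, and a fall in power per arm from 97% to 92% before dropping. No added participants are needed for 80% power per arm. The Sample size section should also say which power the 80% refers to, because power to detect all four effects would be about 79% before dropping and about 69% after.

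### The exploratory sleep and diet interaction models are most naturally read as low/high splits of PSQI and sQ-HPF; keeping the baseline scores continuous would usually use the data better at almost no cost

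*Protocol article*

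**What the plan says.** The Statistical methods section states: "A planned hypothesis-generating (exploratory) subgroup analysis will be conducted considering diet and sleep". The next sentence gives its form: "Interaction models will compare the effectiveness of the sleep module in people with low and high scores on the PSQI". It then sets out a matching comparison for the diet module, by sQ-HPF score. It names no cut-point, does not say which measurement occasion supplies the score, and does not mention a model with the score kept continuous.

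The list of secondary outcomes and Table 1 show that PSQI and sQ-HPF are both collected at baseline and at 6, 12 and 52 weeks. A pre-randomisation value of each full score is therefore available. The baseline score is the natural moderator, although the sentence does not say so.

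The same section sets one threshold for everything: "For all analyses, statistical significance will be indicated by a p value <0.05". The article claims no power for the interaction analysis. Its sample size section covers only the comparison of intervention arms with control.

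**The concern.** A comparison of effectiveness between people with low and high scores, inside a paragraph about subgroup analysis, reads as a two-category moderator. Such a split treats everyone on one side of the cut as alike, makes the answer depend on where the cut falls, and usually weakens a test that is weak to begin with.

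The Statistical methods section plans no other analysis of who gains from the sleep and diet modules, and those modules are what separate intervention groups 2 to 4 from group 1. The trial is sized for arm-versus-control contrasts. Interaction tests therefore start with little power, and arms dropped at the interim would reduce it further. Because the 0.05 threshold applies to all analyses, the results are likely to be read as significant or not. A real gradient could be missed, or a difference reported that owes something to the position of the cut.

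**Working it through.** The article states no information or power figure for this analysis, so there is nothing of its own to reproduce. The check asks what a split would cost under stated assumptions.

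**Inputs from the article.** Outcome SD 5.8. Evaluable participants per arm 21 + 42 = 63 (Sample size section). The sleep module is in groups 2 and 4 and absent from groups 1 and 3; the diet module is in groups 3 and 4 and absent from groups 1 and 2 (Study arms section).

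**Assumptions not in the article.** The score distribution, the cut, the shape of the effect modification, and the pooling of the four intervention arms by module with none dropped, giving 2 × 63 = 126 with the module and 126 without (252 in all).

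**Step 1: information retained.** For a linear interaction, the share of information kept by a two-group split is the squared correlation between the score and its split version. For a normal score with proportion p on one side of the cut, this is

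RE = φ(z_p)² / [p(1 − p)].

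At the median, φ(0)² / 0.25 = 0.1592 / 0.25 = 0.637 (that is, 2/π), a loss of 36.3%. On 252 participants this is like discarding 252 × 0.363 ≈ 91.

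**Step 2: effect on power.** Take an interaction that has 80% power on the continuous score. Its power after the split is Φ[(1.960 + 0.842)·√RE − 1.960]. At the median: 2.802 × √0.637 = 2.235; 2.235 − 1.960 = 0.275; Φ(0.275) ≈ 61%.

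| Split | RE | Loss | Power (80% if continuous) |
|---|---|---|---|
| 50/50 | 0.637 | 36% | 61% |
| 60/40 | 0.622 | 38% | 60% |
| 70/30 | 0.576 | 42% | 57% |
| 75/25 | 0.539 | 46% | 54% |
| 80/20 | 0.490 | 51% | 50% |
| 85/15 | 0.426 | 57% | 45% |
| 90/10 | 0.342 | 66% | 37% |

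**Step 3: scale and simulation check.** With 252 participants, the interaction giving 80% power on the continuous score is 2.802 × 2 × 5.8 / √252 ≈ 2.05 PSFS points per SD of the score. In 4,000 simulated trials of this size, power was 79% with the continuous score and 60% after a median split, in line with the formula.

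**Step 4: other shapes.**
- Uniform score, median split: loss about 25%.
- Exponential score, median split: loss about 52%.
- Normal score, true effect a step exactly at a median cut: the split loses nothing, and a purely linear term on the continuous score keeps only 64%.

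For a normal score with a linear interaction, 36% is thus the smallest loss over all cuts, but it is not a general value.

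**The case against.** Four arguments deserve an answer.

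First, the sentence does not say that the scores are dichotomised. A model with a continuous score, reported at a low and a high value, would also fit the wording. This stands as a possibility, so it should not be stated as fact that the plan splits the scores. It is the less natural reading, however. If it is what is meant, the fix below only makes the sentence say so.

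Second, coding details and cut-points are commonly left to the analysis plan, which the article says is not published alongside it. That is right for cut-points, and their absence is not held against the article here. The point concerns the form of comparison that the article does state. Naming a cut later would not restore what a split loses.

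Third, a reader might infer that a third of the information will be lost, or that a continuous term has no downside. The documents support neither. They give no distribution, cut or shape for the effect modification. The losses examined run from 25% to 66%, and a true step at the cut reverses the comparison. A linear slope and a low-versus-high contrast are also different quantities.

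Fourth, the power illustration depends on pooling arms by module, which the article does not describe, and on a large effect. A 2-point interaction per SD means a 2 × 2 = 4-point change in module effect between −1 SD and +1 SD, equal to the smallest worthwhile effect used for the whole intervention. At 1 point per SD, using simulated standard errors of 0.74 (continuous) and 0.92 (median split), power is about 27% and 19%. This objection stands: the analysis is weak under either coding. The proportional loss in Step 1 depends on neither the effect size nor the number of arms kept.

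**Conclusion.** The point holds as a minor improvement to an exploratory analysis. The text most naturally describes a two-group split of two scores that are available in full at baseline. If the scores are split, a linear effect modification on a normal score loses about 36% of the information at a median cut and more at an unbalanced one. At the median, the loss is about 25% for a uniform score and 52% for an exponential one. There is no loss if the effect is a true step exactly at the cut, but the article gives no reason to expect such a threshold.

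A reader might go further and infer a threat to the trial's conclusions. The documents do not support that: the analysis is labelled hypothesis-generating, no power is claimed for it, no decision about targeting the modules is tied to it, and the primary analysis, sample size and interim rules do not depend on it.

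**What to change.** Replace the low/high comparison with one sentence along these lines: module-by-score interactions will be fitted with baseline PSQI (sleep module) and baseline sQ-HPF (diet module) as continuous variables; non-linearity will be checked, for example with a spline or quadratic term; and module effects with 95% CI will be shown at a low and a high score for display.

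This needs no new data and keeps the low/high presentation that the authors evidently want. Its small cost is an assumption about the shape of the relation, which the non-linearity check is there to address. If the intended model already uses continuous scores, only the wording needs to change.
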